#### Sample size calculation

At least 1056 mother–child pairs will be required (in 16 clusters: 66 mother child pairs per cluster) in each of the intervention and control arms (a total of 2112 mother–child pairs in a total of 32 clusters) to detect a difference of 20% in development delay (assuming 33% suspected development delay^39^ at baseline) at 80% power, 5% level of significance and an intra-class correlation coefficient of 0.15 for maternal education,^13^ allowing for 10% loss to follow-up in each arm.

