## Introduction

Childhood developmental delay is associated with poor subsequent educational attainment, and lower income during adult life, contributing to a cycle of poverty. It is a significant public health concern in many low- and middle-income countries, including Pakistan.^1^

Prevalence of developmental delay in Pakistan has been estimated at around 15%,^2^ even exceeding 30% among children from poorer families.^3^ Developmental delay is strongly linked to undernutrition,^4–6^ and maternal depression.^7^ Indeed, inadequate stimulation in early childhood, and maternal emotional characteristics, are associated with poorer cognitive development.^4^ In one Pakistani study more than one-quarter of new mothers had depression.^8^

There is evidence from low resource settings that programmes to improve infant stimulation and enhanced parenting skills have a beneficial effect on development.^9–11^ In the Caribbean, a parenting intervention integrated into routine primary care was effective in improving cognitive development.^12^ In Pakistan, a development and nutrition intervention delivered by community ‘lady health workers’ in Sindh province, had a significant positive effect on development outcomes.^13^

In poor urban areas of Pakistan, public primary care services are scant, and referral hospitals difficult to access due to distance, expense, and high demand. Primary care is therefore commonly provided by private GP clinics and small community hospitals. These are unregulated, unsupported, and vary in both quality and cost of services. Existing maternal and child health services do not adequately meet the early child development and maternal mental health needs of the population, and nutritional counselling is lacking.^14^ This trial has been designed to investigate the effectiveness and feasibility of integrating an early child development intervention into existing private GP clinic services for poor urban communities, and the aim will be to assess the effectiveness of a primary care intervention in reducing early developmental delay, in poor urban communities of Pakistan, using public–private partnership.

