### Outcomes

#### Primary outcome

##### Suspected developmental delay on screening: ASQ-3 score at 12 months

The Ages and Stages Questionnaire 3^rd^ Edition (ASQ-3) is a childhood developmental screening tool.^22^ By assessing across five developmental domains, it identifies children in primary care who are eligible for further assessment. It is intended that the parent completes the questionnaire, after observing the child at home. However, it can be adapted, for example a parent can be assisted if literacy is poor. Translation and cultural adaptation of the questionnaire is also recommended.^23–25^ Internal and external validity trials of ASQ in a range of populations, cultures, and settings report mixed findings.^24,26–30^ The ASQ-3 questionnaire for children aged 12 months is reported to have a sensitivity of 90% and specificity of 87.5%, when compared to equivalent cutoffs using the Battelle Developmental Inventory-II.^31^ A trial of Hindi ASQ-3 questionnaires in a South Asian population of high and low risk children, found an overall sensitivity of 83.3% and specificity of 75.4%.^32^ The ‘home procedure’ was feasible in India when delivered by non-psychologists, under instruction and supervision. Inter-observer reliability was good. Overall internal validity of the questionnaires was also good, but varied at subscale level.^25^

The ASQ-3 questionnaire has been translated into the Urdu language and adapted to local context for this study. ASQ-3 assessors will have a bachelor’s degree in psychology, and receive training and supervision. Assessment will be conducted at 12 months of age, in private GP clinics. The assessor will record: 1) mother’s responses to the ASQ-3 questionnaire, based on recall and any self-initiated observations; and 2) the assessor’s own on-site observations of specific activities during the assessment session, making use of appropriate toys and props. Mother and assessor scores will be analysed separately, and inter-rater agreement assessed. Final ASQ-3 outcome score will be a composite score of mother response and on-site observations.

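### The stated 80% power and 1056 pairs per arm do not follow from the stated inputs for a fall in delay: power is about 92-93% if the 20% is absolute and about 17% if it is relative

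*Protocol article*

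**What the plan says.** All the inputs stand in one sentence of the protocol article, under Sample size calculation:

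- **Size:** "At least 1056 mother–child pairs will be required (in 16 clusters: 66 mother child pairs per cluster"), in each arm.
- **Target:** "to detect a difference of 20% in development delay (assuming 33% suspected development delay" at what the sentence calls baseline).
- **Error rates and clustering:** "at 80% power, 5% level of significance and an intra-class correlation coefficient of 0.15 for maternal education".
- **Loss to follow-up:** 10% in each arm.

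The sentence does not say whether the 20% is in percentage points or relative to 33%, whether it is a rise or a fall, or whether the test is two-sided. The direction is settled elsewhere. The Introduction gives the aim as reducing developmental delay, and the logic model in Box 2 lists reduced delay at 12 months as the primary outcome.

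**The concern.** A sample size statement should let a reader recover the stated power from the stated inputs, for the effect the trial is looking for. Here there are two natural readings of a 20% reduction from 33%: to 13% (absolute) or to 26.4% (relative). They differ about elevenfold in the number of independent observations needed, so one design cannot have 80% power for both. The check below shows that it has 80% for neither.

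At stake is what the trial can claim. A reader who takes 20% as relative would believe the trial had a four-in-five chance of finding such an effect. A reader who takes it as absolute would be told that 1056 pairs per arm are the minimum, when fewer would do.

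**Working it through.** **Inputs.** From Sample size calculation: reference rate 0.33, ICC 0.15, 16 clusters per arm, 66 recruited per cluster, 10% loss, 5% significance, 80% power. From Study design: 1:1 allocation. Assumed: a two-sided test.

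**1. Reproducing the plan's figure.** Take 20 points upward, 33% to 53%.
- The standard two-proportion formula (pooled variance) gives n = 96 per arm before clustering.
- With 60 analysed per cluster, the design effect is 1 + (60 − 1) × 0.15 = 9.85.
- Clusters per arm: 96 × 9.85 / 60 = 945.6 / 60 = 15.8, rounded up to 16.
- Pairs per arm: 16 × 60 = 960, and 960 × 1.1 = 1056.
- Power of the resulting design is about 81% (pooled) to 82% (unpooled).

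This matches 16 clusters, 66 per cluster and 1056 per arm. No fall did so at 80% power. The variants tried were pooled and unpooled variance, continuity correction, one-sided testing, a t reference and different conventions for loss.

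**2. Effective sample of the stated design.**
- Analysed per cluster: 66 × 0.9 = 59.4; per arm: 16 × 59.4 = 950.4.
- Design effect: 1 + (59.4 − 1) × 0.15 = 9.76.
- Effective pairs per arm: 950.4 / 9.76 = 97.4.

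**3. Absolute fall, 33% to 13%.**
- SE = √[(0.33 × 0.67 + 0.13 × 0.87) / 97.4] = 0.0586.
- Power = Φ(0.20 / 0.0586 − 1.96) = Φ(1.45) = 0.927. Pooled variance gives 0.919; a t reference on 30 df gives 0.91.
- Independent n for 80% power: 7.849 × (0.2211 + 0.1131) / 0.04 = 65.6 (unpooled), 69 (pooled) or 78 (continuity-corrected).
- Pairs to recruit per arm: 65.6 × 9.76 / 0.9 = 711; 69 × 10.75 / 0.9 = 824; 78 × 10.75 / 0.9 = 932. Here 10.75 is the design effect at 66 per cluster. The range is about 710 to 930.

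**4. Relative fall, 33% to 26.4%.**
- SE = √[(0.2211 + 0.264 × 0.736) / 97.4] = 0.0653.
- Power = Φ(0.066 / 0.0653 − 1.96) = Φ(−0.95) = 0.171. Pooled variance gives 0.170; a t reference gives 0.163.
- Independent n for 80% power: 7.849 × (0.2211 + 0.1943) / 0.066² = about 749. That is 749 × 9.76 / 0.9, or about 8,100 pairs per arm.
- Sixteen clusters at ICC 0.15 cannot supply more than 16 / 0.15 = 107 effective pairs, however large each cluster is.

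**5. Difference detectable at 80% power.** Solving for the second rate with 97.4 effective pairs per arm gives 0.159 (pooled) to 0.161 (unpooled): 33% versus about 16%, a fall of about 17 points.

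**6. Sensitivity to the ICC, for 33% versus 13% (unpooled).**

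| ICC | Design effect | Effective pairs per arm | Power |
|---|---|---|---|
| 0.15 | 9.76 | 97.4 | 93% |
| 0.20 | 12.68 | 75.0 | 85% |
| 0.25 | 15.60 | 60.9 | 77% |

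The absolute fall has exactly 80% power at an ICC of about 0.22; the relative fall would need an ICC of about 0.005.

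**The case against.** The strongest reply is that the figures do have a source. The sentence speaks only of a difference, and 20 points added to 33% returns 1056 exactly. That stands, and it has two consequences. A reader might infer that the numbers cannot be derived on any reading; that would be wrong. A reader might also infer from the 17% that the trial is badly underpowered for its target. The exact match argues against this: it points to 20 percentage points as the input, and a relative calculation would have asked for about 8,100 or more pairs per arm. For an absolute fall the error is conservative.

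The match does not rescue the sentence, because a rise to 53% is the opposite of the stated aim. Nor does it prove how the figure arose. An absolute fall at 90% power with one spare cluster also lands there (91 × 9.85 / 60 = 14.9, so 15, plus 1 is 16 clusters of 66), but the protocol states 80% and mentions no spare cluster.

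The surplus should not be exaggerated either. With a continuity correction, 932 pairs, or 14.1 clusters of 66, are needed.

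It is tempting to add that 13% is unattainable, because the Introduction puts national prevalence near 15% and the Hindi ASQ-3 study "found an overall sensitivity of 83.3% and specificity of 75.4"%. The documents do not support that step. The specificity is an overall figure from a mixed-risk sample, and this trial uses an Urdu adaptation and a composite of mother response and observation. The national prevalence need not be on the same measure as a screening rate.

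Calling 33% a baseline rate is loose wording, since children enter by 6 weeks and are assessed with the ASQ-3 at 12 months. It changes no calculation.

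**Conclusion.** The point holds for a reduction in delay. On the stated inputs the design has about 92-93% power for an absolute 20-point fall and about 17% for a relative 20% fall. Neither is the stated 80%, and 1056 per arm is not the requirement in either case. The likely explanation, though not a proven one, is that the 20 points were added to 33% instead of subtracted.

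The conclusion rests on a two-sided 5% test and on ICC 0.15. The protocol gives that ICC for maternal education, not for delay, so every power figure here is conditional on it. The figures also apply to comparing proportions with suspected delay. The Analysis section compares ASQ-3 domain scores by cluster-adjusted t-tests, to which a detectable difference in proportions does not carry over. For that reason a null result should be read from its confidence interval, not against a 17-point threshold.

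**What to change.** Rewrite the sample size paragraph so that it:

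1. says whether 20% is absolute or relative, and that it is a fall;
2. calls 33% the assumed control-arm rate at 12 months;
3. replaces the 80% power claim and the statement that at least 1056 pairs are required with what 16 clusters of 66 per arm and 10% loss deliver at two-sided 5%: about 92-93% power for 33% versus 13%, 80% power for 33% versus about 16%, and about 17% power for a 20% relative fall;
4. states that these figures depend on an ICC of 0.15 taken from maternal education, with power for 33% versus 13% of about 85% at ICC 0.20 and 77% at 0.25;
5. states that they concern the proportion with suspected delay and not the t-tests of domain scores.

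The cost is one paragraph. Recruitment, clusters and follow-up do not change. The price is candour: the paragraph will show low power for a modest relative reduction.

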#### Randomisation

Simple randomisation will be performed by drawing from a hat, by a member of the host research organisation not involved in the study. Stratification by districts (Rawalpindi and Lahore) has not been done as both share similar characteristics being major cities in the province of Punjab. Nevertheless clinic size, if not equally distributed between both arms by randomisation, will be taken care of in modeling (GEE and GLMM as mentioned above).

#### Blinding

Due to the nature of the intervention, participants will not be blinded. ASQ-3 assessors will be blinded to allocation of participants. Members of the research team undertaking 12-month maternal PHQ-9 assessments will not be blinded.

#### Ethics and dissemination

Verbal consent will be obtained from community leaders. Written consent will be taken from the clinic staff, and verbal consent from participating mothers. Mothers can withdraw consent at any time. Clinical referrals will be made to local specialist services where appropriate.

The trial results will be published in open access peer-reviewed journals. Results will be communicated to key government and non-government stakeholders at national level, with a view to scale-up if the intervention is effective, feasible and acceptable.

The SPIRIT checklist has informed the preparation of this protocol.^40^

#### Process evaluation

A process evaluation will accompany the trial, following MRC Guidance.^41^ Mixed methods will be used to explore intervention implementation, mechanisms of impact, and context. Quantitative data will be extracted from study records, and descriptive analyses presented. Qualitative data will be gathered from in-depth interviews. Purposive sampling will be used, for maximal variation in views and experience. Interviews will be audiorecorded and transcribed in Urdu. Framework Approach will be used in analysis.^42^

#### Economic evaluation

Data will be collected on costs incurred by the intervention to inform incremental cost-effectiveness ratio (ICER) analysis of the health services cost. The study will account for both provider and client perspectives, and will consider recurrent costs incurred should the intervention be implemented without study resources. The marginal costs of the intervention, to both public and private providers will be estimated, as well as costs to participating mothers. An economic survey of participating mothers will be conducted at 12 months to determine costs of care.

## Discussion

### Summary

A clustered randomised controlled trial will assess the effectiveness of an early child development counselling intervention delivered at private GP clinics, in poor urban communities of Pakistan. Primary outcome is the developmental delay at 12 months (ASQ-3 scores). Secondary outcomes are stunting rate, and maternal depression (PHQ-9 score).

### Strengths and limitations

The intervention was developed in consultation with local experts, following a period of formative research. It will be implemented in the existing private GP clinic setting, in the context of a public–private partnership. Anticipated challenges of the proposed research include:

Follow-up appointments are not usual practice in the existing primary care context in Pakistan. Non-adoption by providers and patients is a therefore a possible challenge. Some trial supervision will be provided to clinics by research staff, however the aim is to assess real-life implementation. Non-attendance by mothers for follow-up visits may lessen measured effectiveness of the intervention.Most patient records are stored in primary care for a maximum of 3 days, if at all. Both intervention and control clusters will be instructed to keep clinic records, which is a new concept, and may present challenges.Providers may not implement the intervention according to the trial protocol, for example if there is insufficient time during the clinic visit. This may reduce the effectiveness of the intervention, and will be explored in the process evaluation.Mothers in the intervention arm will be more familiar with child development activities than those in the control arm, which may bias recall of developmental achievements at 12 months. On-site observations of development will to try to reduce this bias.

### Comparison with existing literature

To the authors’ knowledge this study is the first to assess an early child development intervention, delivered in private GP clinics in Pakistan.

### Implications for practice

Private sector engagement in education and healthcare delivery is a national strategy for universal coverage of health and social services in Pakistan, and the proposed intervention offers an alternative to a home-based delivery model of early child development care. If effective, service provision at private clinics may offer a more feasible option for populations in poor urban settings, where they are by far the most accessible provider of health care.
